### Sample Size

TASC data from January 2003 to May 2005 demonstrated that 35% of patients had a mRS ≥2 at hospital discharge, and the mean hospital discharge mRS was 2, with a standard deviation of 2. A sample of 250 per group would allow detection of a difference between groups of 12% (35% versus 23%) for the proportion of patients with death or disability (≥2 on the mRS) and a clinically meaningful difference in mean mRS of 0.5 (from 2 to 1.5, equivalent to a 25% change in mean score) with 80% power and a 5% (two-sided) significance level. This sample would also allow detection of differences between groups of at least 13% for binary outcomes and one-quarter of a standard deviation for continuous outcomes, with 80% power and a 5% (two-sided) significance level. Assuming a loss to follow-up of 10%, an effective sample size of 280 participants per group is required to be recruited. These calculations assume independent observations. We devised a table to demonstrate statistical power according to various defensible estimates of intra-cluster correlation co-efficients (ICCs) for these two patient outcomes (Table 2). Estimated ICCs range from 0.01 to 0.03 [52]. We anticipate a design effect of 1.85, thus aim to recruit 520 patients per group (1,040 in total).

**Table 2 T2:** Effective sample size, assuming different magnitudes of intracluster correlation (ICC)^

**ICC**	**Design Effect**	**Number of patients per group**	**Total number of patients required**
0	1	280	560
0.01	1.4	400	800
0.015	1.85	520	1040
0.02	2.6	730	1460
0.03	4.4	1230	2460

^ 80% power at alpha = 0.05; nine ACU's per group; adjusted for loss to follow-up of 10%

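### Table 2 does not follow from the plan's own inputs: the ICC 0.01 to 0.02 rows are too high and the ICC 0.03 row is too low

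*Protocol article*

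**What the plan says.** All of this is in the Sample Size section of the protocol article.

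- Requirement before clustering: "A sample of 250 per group would allow detection of a difference between groups of 12% (35% versus 23"%), and a 0.5-point difference in mean mRS, "with 80% power and a 5% (two-sided) significance level". The SD behind the second comparison is given as "the mean hospital discharge mRS was 2, with a standard deviation of 2", so 0.5 points is 0.25 SD.
- Allowance for loss: "Assuming a loss to follow-up of 10%, an effective sample size of 280 participants per group is required to be recruited". The next sentence adds "These calculations assume independent observations".
- Target: "We anticipate a design effect of 1.85, thus aim to recruit 520 patients per group (1,040 in total").
- Table 2 starts from 280 per group at ICC 0. It then prints 400 (design effect 1.4), 520 (1.85), 730 (2.6) and 1,230 (4.4) at ICC 0.01, 0.015, 0.02 and 0.03. Its footnote gives "nine ACU's per group; adjusted for loss to follow-up of 10"%. The text gives 0.01 to 0.03 as the range of estimated ICCs.

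The text does not say which cluster size enters the design effect, but the printed figures reveal it.

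**The concern.** The design effect describes the variance of the data that are analysed. The plan expects 10% of recruits to give no 90-day outcome. Those patients add neither information nor within-ASU correlation to the comparison, so they do not belong in its cluster size. With nine ASUs per group fixed, the mistake feeds on itself: a larger number recruited raises the patients per ASU, which raises the design effect, which raises the number required. The discrepancy therefore grows with the ICC.

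The top row of the ICC range has a different problem, because its figure does not follow from the table's own method either.

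Table 2 is where a reader sees how the required size depends on the ICC. At present it is too pessimistic in the middle of the stated range and too optimistic at the top of it.

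**Working it through.** **Inputs** (protocol article, Sample Size and Table 2): n0 = 250 analysed per group under independence; k = 9 ASUs per group; loss 10%; difference 0.25 SD; two-sided 5% level; 80% power.

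**Formula.** With N patients per group in k equal clusters, DE = 1 + (N/k − 1) × ICC. Setting N = n0 × DE and solving gives

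N = n0 × (1 − ICC) / (1 − n0 × ICC / k).

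**Step 1: reproduce the printed rows.** Take n0 = 280, so that the cluster size is the recruited one.

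- ICC 0.01: 280 × 0.99 / (1 − 0.3111) = 402, DE 1.44 (printed 400, 1.4)
- ICC 0.015: 280 × 0.985 / (1 − 0.4667) = 517, DE 1.85 (printed 520, 1.85)
- ICC 0.02: 280 × 0.98 / (1 − 0.6222) = 726, DE 2.59 (printed 730, 2.6)
- ICC 0.03: 280 × 0.97 / (1 − 0.9333) = 4,074, DE 14.55 (printed 1,230, 4.4)

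The first three agree after rounding. A direct check confirms the cluster size: 520/9 = 57.8 and 1 + 56.8 × 0.015 = 1.85; 730/9 = 81.1 and 1 + 80.1 × 0.02 = 2.60.

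The last row does not agree. Under the same method, ICC 0.025 gives 280 × 0.975 / (1 − 0.7778) = 1,228 with DE 4.39, which matches the printed 1,230 and 4.4.

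**Step 2: recompute at the analysed cluster size.** Take n0 = 250, then divide by 0.9.

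| ICC | Analysed per group | DE | Recruited per group | Printed | Printed relative to recomputed |
|---|---|---|---|---|---|
| 0.01 | 342.7 | 1.37 | 381 | 400 | +5% |
| 0.015 | 422.1 | 1.69 | 469 | 520 | +11% |
| 0.02 | 551.3 | 2.21 | 612.5 | 730 | +19% |
| 0.03 | 1,455 | 5.82 | 1,617 | 1,230 | −24% |

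By the normal approximation 250 gives 79.8% power for 0.25 SD, and 252 are needed for 80%. Starting from 252, the recruited numbers are 385, 476, 624 and 1,698.

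**Step 3: what 520 recruited per group delivers at ICC 0.015.** Analysed: 520 × 0.9 = 468. Cluster size: 468/9 = 52. DE = 1 + 51 × 0.015 = 1.765, not 1.85. Effective size: 468/1.765 = 265. Normal-approximation power for 0.25 SD is about 82%.

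**Step 4: what 1,230 recruited per group delivers at ICC 0.03.** Analysed: 1,107. Cluster size: 123. DE = 1 + 122 × 0.03 = 4.66. Effective size: 238, below 250. Power for 0.25 SD is about 78%.

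**Step 5: how firm the margin at 520 is.** Two assumptions that the documents do not state were varied, both at ICC 0.015.

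- Reference distribution: a t distribution with 18 − 2 = 16 cluster-level degrees of freedom, with equal ASUs, gives about 77% power at an effective size of 265.
- Unequal ASUs: with DE = 1 + ((1 + CV²) × 52 − 1) × 0.015, where CV is the coefficient of variation of ASU size, the effective size is 255 at CV 0.3, 248 at CV 0.4 and 239 at CV 0.5.

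**The case against.** The strongest reply is that nothing needs to change in the trial. Using recruited patients per ASU is conservative at the chosen ICC, the target of 1,040 is not too small on the plan's own formula, and no hypothesis or analysis is put at risk. That stands, and it limits the point to correcting stated figures.

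A second reply concerns the cause. A reader might infer that the error is adding the loss before the design effect. At a fixed cluster size the order makes no difference: 250/0.9 × 1.85 and 250 × 1.85/0.9 are both 513.9. The excess comes from the recruited cluster size combined with a fixed number of ASUs, plus rounding (278 taken as 280, 517 as 520). This reply is correct.

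A third reply concerns the reserve. A reader might infer that 520 per group carries spare capacity, for instance that it keeps 250 effective patients up to an ICC of about 0.017 ((468/250 − 1)/51), or that recruitment could be cut to 469. The documents do not support either. The calculation rests on a normal approximation and equal ASUs. The trial has only 18 ASUs on the table's footnote, and the ASU randomisation section itself expects high and low recruiters. Under the 16-degrees-of-freedom assumption, power at 469 is about 75%, and about 595 per group would be needed for 80%.

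**Conclusion.** Table 2 is wrong on the plan's own inputs, in two directions. The ICC 0.01 to 0.02 rows are too high by about 5%, 11% and 19%, because the loss-inflated 280 is carried through a design effect at the recruited cluster size. The ICC 0.03 row is about 24% too low, and its entries belong to ICC 0.025 under the table's own method. It would therefore be a mistake to read the whole table as overstated.

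The error in the middle rows is conservative at the chosen target and does not threaten the trial's validity. The figures rest on nine equal-sized ASUs per group, 10% loss spread evenly over ASUs, and a normal approximation. Using 252 instead of 250 shifts them slightly and changes no conclusion. The sizes of the degrees-of-freedom and unequal-ASU effects depend on assumed values, but they are enough to show that the margin at 520 should not be relied on.

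**What to change.** Keep 1,040.

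1. Recompute every row of Table 2, including ICC 0.03, from 250 (or 252) analysed per group, with DE = 1 + (m − 1) × ICC at the analysed cluster size m, and then divide by 0.9.
2. Replace the description of 280 as an effective sample size by: *250 analysed, 278 recruited, per group before clustering* (252 and 280 if 252 is used).
3. Give the design effect at 520 recruited per group as 1.77 at ICC 0.015.
4. Do not state a reserve or an ICC that 520 covers. Say instead that the figures use a normal approximation with equal-sized ASUs, and that the apparent margin at 520 disappears with about 16 cluster-level degrees of freedom or moderately unequal ASU sizes.

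The cost is a corrected table and a few sentences. Recruitment does not change.

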#### ASU randomisation

Once the baseline patient cohort 90-day outcome data have been collected, participating ASUs will be stratified and randomised. The project officer (SD) will first stratify ASUs according to their category classification (A or B) and then, by referring to absolute numbers of patients recruited at baseline, describe each as a 'high recruiter' or 'low recruiter'. Recruitment numbers will be included as a randomisation strata to maximise the chance of similar sample size in the intervention and control groups. Stratification details will be provided in a de-identified form to an independent statistician located offshore and not otherwise involved in the study for randomisation within strata, this will be generated using random number generating software[29]. Allocation will be based on clusters (ASUs) rather than individuals, and the sequence will be concealed until the intervention is assigned. Thus, generation of the allocation sequence and assigning of ASUs to either intervention or control group will be undertaken by the offshore independent statistician. To strengthen our methodological rigour, personnel who recruit patients (CRAs), research interviewers who undertake the CATIs, and the offshore statistician who undertakes randomisation all will be independent and also blinded to all other components of the study design. A flow diagram further outlining the trial design is shown in Figures 1 and 2.

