### Data Analyses

Blinded outcome assessment will be undertaken for all analyses of primary and secondary outcome measures. Data will be analysed using Stata [51]. Intention-to-treat analysis will applied [26].

To examine potential response bias, demographic characteristics for eligible consenting and non-consenting patients will be compared using the chi-square test for categorical variables (sex, stroke sub-type, and stroke severity) and the t-test (or a non-parametric equivalent) for the continuous variable of age.

For all patient-related outcome analyses, we will use cluster-specific methods. Dichotomous outcomes (death or disability [mRS ≥2] at 90 days; swallowing screen within 24 hours of admission) will be compared between intervention and control groups using the chi-square test. Continuous outcomes – level of disability (mRS score), dependency (Barthel Index), health status (MCS and PCS of SF-36), improved glycaemic control, and improved temperature control – will be compared between the two intervention groups using the t-test. The survey (svy) commands in Stata will be used to adjust for clustering of patients within ASUs. Multilevel modelling (logistic or linear as appropriate) will be used to compare primary outcomes – death or disability (mRS or ≥2) at 90 days, level of disability (mRS score), dependency (Barthel Index), and health status (MCS and PCS of SF-36) – between groups while adjusting for potential confounders or effect modifiers and for the cluster study design. These analyses will be undertaken in the Stata statistical package [51].

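### At ICC 0.015, 1,040 patients in nine ASUs per group give about 77% power, not 80%, for the 0.25 SD primary hypotheses with equal units, and less if recruitment is uneven; the death-or-disability comparison has some slack

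*Protocol article*

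**What the plan says.** The Sample Size section starts from 250 independent patients per group, said to detect "a difference between groups of 12% (35% versus 23"%) for death or disability and also "a clinically meaningful difference in mean mRS of 0.5 (from 2 to 1.5, equivalent to a 25% change in mean score"). Both claims are for a two-sided 5% test at 80% power. It reports that "the mean hospital discharge mRS was 2, with a standard deviation of 2", so 0.5 units is 0.25 SD. The Primary hypotheses section sets the Barthel Index and SF-36 targets at 0.25 SD as well.

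Allowing for 10% loss gives 280 per group. Clustering then leads to the target: "We anticipate a design effect of 1.85, thus aim to recruit 520 patients per group (1,040 in total"). In Table 2 this is the row for ICC 0.015, and the footnote reads "80% power at alpha = 0.05; nine ACU's per group; adjusted for loss to follow-up of 10"%.

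Under ASU randomisation, the project officer will use baseline recruitment numbers to "describe each as a 'high recruiter' or 'low recruiter"', and this label becomes a randomisation stratum. Its stated purpose is to keep the two groups similar in total size. The article gives no per-unit target, size range or CV.

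For the analysis, "The survey (svy) commands in Stata will be used to adjust for clustering of patients within ASUs", and multilevel models are planned for the primary outcomes.

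**The concern.** Two features of the design are missing from the calculation.

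- **Few units.** With 18 ASUs in two groups, the treatment comparison is judged against variation between ASUs, on about 18 − 2 = 16 degrees of freedom. The calculation uses normal quantiles, as if there were many units.
- **Unequal units.** The design effect formula behind Table 2 takes every ASU to be the same size. The plan stratifies on recruitment because it expects the units to differ. That stratification balances the group totals. It does not make the ASUs equal in size, so the precision lost to uneven units remains.

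The 80% figure is the basis for 1,040 patients. If true power for three of the four primary hypotheses is lower, a null result on mean mRS, Barthel Index or SF-36 would be taken as stronger evidence of no effect than the design can support.

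**Working it through.** **Inputs from the protocol.** Two-sided alpha 0.05; 0.25 SD (0.5 on an SD of 2); 35% versus 23%; 280 per group after 10% loss; nine ASUs per group; ICC 0.015; 520 recruited per group. I take the 520 as the patients compared between groups after the intervention.

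**Assumption.** The CV of unit size is not given. If half the units are high and half low recruiters in ratio r, then CV = (r − 1)/(r + 1). This gives 0, 0.333, 0.5 and 0.6 for r = 1, 2, 3 and 4.

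**Step 1: reproduce the plan's figure.**
- Mean unit size 520/9 = 57.8, so the design effect is 1 + (57.8 − 1) × 0.015 = 1.85.
- Solving for N with nine units: N = 280(1 − ICC)/(1 − 280 × ICC/9) = 517, against 520 stated.
- The same formula gives 402 and 726 at ICC 0.01 and 0.02, against 400 and 730 in Table 2.

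These rows therefore use equal units. The ICC 0.03 row does not follow from this formula, but nothing here depends on it.

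**Step 2: slack before clustering.** With 250 independent patients per group and a normal reference:
- 0.25 SD: 0.25 × √(250/2) = 2.795, power 79.8%.
- 35% versus 23%: 0.12/√[(0.35 × 0.65 + 0.23 × 0.77)/250] = 2.983, power 84.7%.

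Only the second has room to lose.

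**Step 3: power of 1,040.** Analysed per group: 520 × 0.9 = 468, or 52 per unit.
- Design effect: DE = 1 + [(1 + CV²) × 52 − 1] × 0.015.
- Effective n per group: n_eff = 468/DE.
- Noncentrality: 0.25 × √(n_eff/2) for the 0.25 SD outcomes, and 0.12/√(0.4046/n_eff) for the composite.
- The t reference has 16 df, critical value 2.120.

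| High:low | CV | DE | n_eff | 0.25 SD, normal | 0.25 SD, t 16 df | 35% v 23%, t 16 df |
|---|---|---|---|---|---|---|
| 1:1 | 0 | 1.765 | 265 | 82.1% | 77.1% | 82% |
| 2:1 | 0.333 | 1.852 | 253 | 80.2% | 75% | 80% |
| 3:1 | 0.5 | 1.960 | 239 | 78.0% | 73% | 78% |
| 4:1 | 0.6 | 2.046 | 229 | 76.2% | 71% | 76% |

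**Step 4: separate the two causes for 0.25 SD.** With equal units, moving from the normal to the t reference costs 82.1 − 77.1 = 5 points. On the t reference, uneven recruitment then costs about 2 points at 2:1, 4 at 3:1 and 6 at 4:1. On a normal reference with 52 analysed per unit, unequal size alone takes power below 80% only above a CV of about 0.36. If the recruited size of 57.8 is kept in the design effect, as Table 2 does, that threshold is about 0.12.

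**Step 5: recruitment by Table 2's own method.** N = 280(1 − ICC)/[1 − 280 × ICC × (1 + CV²)/9] gives 573, 662 and 755 per group at 2:1, 3:1 and 4:1. This shows how steep the effect is with nine units. It is not a proposed target.

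**The case against.** A reader might infer that uneven recruitment by itself means that 1,040 patients miss 80% power on every primary hypothesis. The protocol does not support that, for three reasons.

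- A high/low label can be put on any spread, small or large, so the ratios above are scenarios. This stands.
- The death-or-disability comparison has slack. It keeps 80% up to about 2:1 on 16 df, and to a CV above 0.5 on a normal reference. This stands.
- Table 2 puts recruited rather than analysed unit size into the design effect, which is conservative. Done consistently, a 2:1 imbalance leaves the 0.25 SD outcomes at 80.2% on a normal reference. This stands, and it is why the small number of units has to be named as the main cause at modest imbalance.

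Other offsets help less.

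- Twenty category A and B ASUs are eligible. If all took part (46.8 analysed per unit, equal sizes), DE = 1 + 45.8 × 0.015 = 1.687, n_eff = 277 and noncentrality is 2.94. On 18 df the power is 79.5%, still just short.
- A multilevel model that weights units efficiently recovers about 1 to 2 points (74% at 3:1). Adjusting for severity and pre-morbid mRS may reduce unexplained variance, but the protocol claims no gain from it.
- The ICC matters more. With equal units and 16 df, 0.25 SD power is 83% at ICC 0.01 (DE 1.51) and 62% at 0.03 (DE 2.53). Table 2 shows that uncertainty openly, however. Degrees of freedom and unit-size variation appear nowhere in it.

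The arithmetic of 1.85 and 520 is right for its formula. What is wrong is the formula's fit to this design.

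**Conclusion.** The point holds for the 0.25 SD primary hypotheses. At the planned ICC of 0.015, the stated 80% is about 77% even with equal units, and that needs no assumption about recruitment. It becomes 75%, 73% or 71% under assumed imbalances of 2:1, 3:1 or 4:1.

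For 35% versus 23% the claim of 80% survives equal units (82%) and about 2:1 (80%). It fails modestly beyond that (78% and 76%).

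These figures rest on nine ASUs per group, 10% loss spread evenly over the units, the same ICC for every outcome, and a t reference on about 16 df. The exact degrees of freedom depend on how the strata enter the analysis. The shortfall is a few points. It is worth correcting because 80% is the stated basis for the trial's size.

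**What to change.** In the Sample Size section and Table 2:

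1. Replace the design effect by 1 + [(1 + CV²) × mean unit size − 1] × ICC, and say whether unit size means recruited or analysed patients.
2. Use a t reference on 16 df for nine ASUs per group.
3. Restate the power of 1,040 patients separately for the 0.25 SD outcomes and for death or disability. Until a CV is known, give about 77% and 82% for equal units, with 71–75% and 76–80% as the range for 2:1 to 4:1.
4. Before post-intervention recruitment starts, replace the assumed CV by the one from the baseline counts per ASU, which the randomisation procedure already uses.

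The cost is a recalculated table and a slightly less favourable stated power. No patients need be added, and the planned analysis need not change.

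### Table 2's row for an ICC of 0.03 carries the values for an ICC of 0.025; the table's own method gives about 4,070 patients per group at 0.03, not 1,230

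*Protocol article*

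**What the plan says.** The Sample Size section starts from independent observations: "A sample of 250 per group would allow detection" of a "difference between groups of 12% (35% versus 23" per cent) in death or disability and of a 0.5-unit difference in mean mRS, "with 80% power and a 5% (two-sided) significance level". For the mRS it states that "the mean hospital discharge mRS was 2, with a standard deviation of 2", so 0.5 units is 0.25 SD. Allowing for 10% loss to follow-up, it reaches 280 per group.

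It then says "Estimated ICCs range from 0.01 to 0.03", and Table 2 shows the sample needed at ICCs of 0, 0.01, 0.015, 0.02 and 0.03. The footnote reads "80% power at alpha = 0.05; nine ACU's per group; adjusted for loss to follow-up of 10" (per cent). The last row reads "0.03 4.4 1230 2460": ICC, design effect, patients per group, total. The plan adopts a design effect of 1.85, which is the 0.015 row, and aims for 520 per group.

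**The concern.** With the number of clusters fixed, more patients means larger clusters, and the design effect grows with cluster size. The required sample therefore climbs steeply as the ICC rises. Going from an ICC of 0.02 to 0.03, Table 2 shows only a move from 730 to 1,230 per group, which is too gentle for nine units per group.

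The row matters because 0.03 is the top of the plan's own ICC range, so it tells the reader what the worst stated case would require. As printed, that case looks like a larger but ordinary trial of 2,460 patients. If the row is wrong, the table hides how close nine units per group come to the point where recruiting more patients no longer helps.

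**Working it through.** **Inputs (all from the Sample Size section and Table 2).** Two-sided alpha 0.05; power 80%; mRS difference 0.5 with SD 2; 35% versus 23%; loss to follow-up 10%; nine units per group; ICCs as tabulated.

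**Base figure.** The 0.25 SD difference needs 252 per group, and 252/0.9 = 280, the plan's figure. The 35% versus 23% contrast needs fewer (224), so the mean mRS sets the base.

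**Table method.** With N recruited per group in nine units:

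- design effect DE = 1 + (N/9 − 1) × ICC
- N = 280 × DE
- solved: N = 280 × (1 − ICC) / (1 − 280 × ICC/9)

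| ICC | Recomputed N (DE) | Printed N (DE) |
|---|---|---|
| 0 | 280 (1.00) | 280 (1) |
| 0.01 | 402 (1.44) | 400 (1.4) |
| 0.015 | 517 (1.85) | 520 (1.85) |
| 0.02 | 726 (2.59) | 730 (2.6) |
| 0.025 | 1,228.5 (4.39) | not listed |
| 0.03 | 4,074 (14.55) | 1,230 (4.4) |

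The first four printed rows reproduce. At 0.03, N = 280 × 0.97 / (1 − 0.9333) = 271.6/0.06667 = 4,074 per group, about 8,150 in total.

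**Internal check of the printed row.** 1,230/9 = 136.7 per unit. At ICC 0.03, DE = 1 + 135.7 × 0.03 = 5.07, not 4.4, and 280 × 5.07 is about 1,420, not 1,230. Working back from the printed values, (4.4 − 1)/135.7 = 0.025.

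**Sensitivity of the 0.03 figure.** The effective sample in nine units cannot exceed 9/0.03 = 300 per group. The 280 required is close to that limit, so small changes in the base move N a great deal.

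- Unrounded base 250/0.9 = 277.8: about 3,640 per group.
- Attrition taken out of the cluster size (250 to 252 analysed, then divided by 0.9): about 1,620 to 1,700. This is not the table's method, because it gives 469 to 476 where 520 is printed and 613 to 624 where 730 is printed.
- Ten units per group: about 1,080 to 1,700 depending on the base. This contradicts the footnote and misses the 0.01, 0.015 and 0.02 rows.

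**Power.** Effective analysed patients per group are e = 0.9N/DE. With Φ the standard normal distribution function:

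- 0.25 SD: Φ(0.25 × √(e/2) − 1.96)
- 35% versus 23%: Φ[(0.12√e − 1.96√(2 × 0.29 × 0.71)) / √(0.35 × 0.65 + 0.23 × 0.77)]

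| N per group | ICC | DE | e | 0.25 SD | 35% v 23% |
|---|---|---|---|---|---|
| 1,230 | 0.025 | 4.39 | 252 | 80% | 85% |
| 1,230 | 0.03 | 5.07 | 218 | 74% | 79% |
| 520 | 0.015 | 1.85 | 253 | 80% | 85% |
| 520 | 0.02 | 2.14 | 219 | 74% | 79% |
| 520 | 0.03 | 2.70 | 173 | 64% | 69% |

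If attrition shrinks the clusters, 1,230 at ICC 0.03 leaves 1,107 analysed, 123 per unit, DE 4.66 and e = 238. Power is then 78% for 0.25 SD and 82% for 35% versus 23%.

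**The case against.** Four points can be made for the plan.

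- **The numbers may be right and only the label wrong.** The printed 1,230 and 4.4 are what the method gives at 0.025. This stands as the likeliest explanation, though the article does not say which value was meant. Relabelling alone is not enough, because the text takes the ICC range up to 0.03 and the top of that range would then have no row.
- **The 4,070 is fragile.** This also stands. A reader might infer a firm 3.3-fold understatement (4,074/1,230), but that ratio holds only on the table's convention with the base rounded to 280. If attrition shrinks the clusters, it is about 1.3-fold (1,617/1,230). What survives is that every nine-unit calculation at 0.03 exceeds 1,230.
- **The power shortfall is not uniform.** A reader might infer that 1,230 per group misses 80% for both outcomes. For 35% versus 23% it gives 79% to 82%, so it meets the target or misses it by about a point. The shortfall is clear only for 0.25 SD (74% to 78%), the outcome that sets the base.
- **Nothing adopted rests on the row.** The target of 520 comes from the 0.015 row. This stands, and it limits the severity.

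**Conclusion.** The ICC 0.03 row of Table 2 is wrong as labelled. Its values belong to an ICC of 0.025. At 0.03 the table's method gives about 4,070 per group (DE about 14.6, about 8,150 in total). This rests on nine equal units per group, a base of 280, and loss to follow-up applied before the cluster size is set, as in the other rows. The power figures use normal approximations.

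Two stronger readings go too far. One is that the recruitment target is miscalculated: 520 per group reproduces at the design effect the plan adopts. The other is that an ICC of 0.03 makes the trial unachievable outright: that is a fair description on the table's convention, but not if attrition is allowed to shrink the clusters, where about 1,620 to 1,700 per group would do. The error is in a stated sensitivity figure, of moderate to minor severity. Its practical effect is to make the top of the plan's ICC range look easier to accommodate than it is.

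**What to change.** 1. Relabel the existing row (4.4; 1,230; 2,460) as ICC 0.025.
2. Give ICC 0.03 its own row: design effect about 14.6, about 4,070 per group and about 8,150 in total, or mark it as not practically achievable with nine units per group. Note that the figure is sensitive to rounding because the effective sample is capped at 300 per group.
3. Add one sentence on the power of the planned 520 per group: at ICC 0.02 about 74% for 0.25 SD and 79% for 35% versus 23%; at ICC 0.03 about 64% and 69%.

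The cost is one relabelled row, one new row and one sentence. The target of 520 per group, the design and the analysis stay as they are.
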